### Clinical Event Committee

An independent CEC is proposed to review the primary efficacy and safety end points. The CEC will review cases of interest to determine if they meet the criteria defined in this charter. Causality assessments will not be made by the CEC, nor will the committee possess governance authority. The CEC will be blinded where possible regarding all information relating to the randomisation group. The CEC will include four cardiovascular physicians who have expertise in the diagnosis and treatment of cardiovascular disorders and in the medical aspects of clinical trials. The CEC will have a Chairman and coordinator to assist with preparation of de-identified source clinical data, reports and communication with the Trials Unit. The CEC will follow a predetermined adjudication charter.

*Primary outcome*: The primary outcome is the postrandomisation rate of major adverse events (co-primary composite outcome), including one composite outcome for *efficacy* and one composite outcome for *safety*. The comparison between the incidences of each outcome according to treatment group will assess the between-group difference in the proportion of major adverse events in patients allocated to non-invasive conservative management compared with invasive management. The trial is designed to assess the feasibility of recruiting and randomising such a population but is not powered to detect a between-group difference in clinical outcomes.

*Primary efficacy outcome*: Defined as all-cause mortality, rehospitalisation for refractory ischaemia/angina, MI or hospitalisation for HF. The end points will be assessed during the study until the final randomised patient has completed 18 months follow-up.

*Primary safety outcome*: Defined as bleeding (Bleeding Academic Research Consortium (BARC) types 2–4),^36^ stroke, procedure-related MI (type 4a, universal definition), worsening renal function or haemodialysis during the index hospitalisation.

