**Methods and analysis:**

60 patients will be enrolled in a randomised clinical trial in 4 hospitals. A screening log will be prospectively completed. Patients not randomised due to lack of eligibility criteria and/or patient or physician preference and who give consent will be included in a registry. We will gather information about screening, enrolment, eligibility, randomisation, patient characteristics and adverse events (including post-discharge). The primary efficacy outcome is the composite of all-cause mortality, rehospitalisation for refractory ischaemia/angina, myocardial infarction and hospitalisation for heart failure. The primary safety outcome is the composite of bleeding, stroke, procedure-related myocardial infarction and worsening renal function. Health status will be assessed using EuroQol 5 Dimensions (EQ-5D) assessed at baseline and 6 monthly intervals, for at least 18 months.

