### Advances in interventional management

PCI continues to evolve through advances in technologies and technical skills. In recent years, specialist techniques have developed with ‘antegrade’ and ‘retrograde’ approaches to recannalise chronic totally occluded coronary arteries.^21^ The potential benefits of new approaches for complex PCI in CABG patients merit prospective evaluation in the future trial.

*Overall hypothesis*: Considering efficacy, safety and health economics, a routine conservative (and selectively invasive) approach in patients with NSTE-ACS with prior CABG will be an acceptable alternative to the routine invasive approach, which is the current standard of care.

*Active efficacy hypothesis*: Compared with a routine non-invasive approach, a routine invasive approach in patients with NSTE-ACS with prior CABG is associated with a lower rate of all-cause mortality, recurrent MI or HF.

*Active safety hypothesis*: Compared with a routine invasive approach, a routine non-invasive approach in patients with NSTE-ACS with prior CABG is associated with a lower rate of adverse events related to safety during the index hospitalisation.

*Health economics hypothesis*: Compared with a routine invasive approach, a routine non-invasive approach is cost-saving and associated with reduced resource utilisation.

*Pilot study objectives to inform a potential future clinical trial*: To obtain information on: (1) the absolute number of patients admitted with an NSTE-ACS and a prior history of CABG; (2) number of screen failures (and the reasons); (3) enrolment rate; (4) randomisation rate; (5) reasons for failure to obtain informed consent in potentially eligible patients or failure to randomise (clinical registry); (6) medical profile, including comorbidity; (7) revascularisation rates with PCI or CABG; (8) duration of index admission; (9) serious adverse events, including rehospitalisation (and the causes), and death (and the causes), as adjudicated by a Clinical Event Committee (CEC) blinded to treatment group assignment. Some pivotal clinical trials excluded patients with prior CABG, which we think qualifies the current guidelines that recommend invasive management in NSTE-ACS and prior coronary disease (including prior CABG).^12^
^13^

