### Definitions of adverse events

*Death*: All-cause, sudden cardiac death, death due to MI, death due to HF, death due to stroke, death due to extra-axial haemorrhage, death due to cardiovascular operation, death due to other cardiovascular cause (eg, infective endocarditis), presumed cardiovascular death (undetermined cause of death), non-cardiovascular death.^37^
^38^

*Procedure-related MI:* According to the universal definition of MI. A postprocedure ECG will enable diagnosis of Q versus non-Q MI.

*Stroke* is defined as the presence of a new focal neurological deficit thought to be vascular in origin, with signs or symptoms lasting more than 24 h; subdural haemorrhage.

*Major bleeding* is defined according to the BARC criteria.^36^

*Worsening renal function* is defined as deterioration in estimated glomerular filtration rate ≥25% of baseline during the index admission.

*Follow-up and timing of outcome evaluations*: Follow-up (via telephone contact, clinic visits, letter) with completion of quality of life assessments (EQ-5D) will be maintained at six monthly intervals until a minimum of 18 months follow-up has been reached for the final recruited patient. Data will be held for up to 20 years to enable long-term follow-up analyses.

Following randomisation, clinical assessments will involve gathering information from the standard-of-care clinical reviews (end of hospitalisation, 30–42 days and 1 year) and also from clinical contacts recorded in the patients’ medical records. In West of Scotland hospitals, a single system of electronic patient records is used for all hospital attendances and correspondence with primary care.

*Cross-over*: A cross-over between groups is defined as a change of treatment strategy from invasive to non-invasive management, or vice versa. In addition, we predefined cross-over as occurring within 30 days after randomisation.

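### The co-primary safety composite has no death component, so an in-hospital death without another listed component counts as free of a safety event

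*Protocol article*

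**What the plan says.** The section Clinical Event Committee sets up a co-primary outcome with one composite for efficacy and one for safety.

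- **Safety composite:** "Defined as bleeding (Bleeding Academic Research Consortium (BARC) types 2–4"), together with "stroke, procedure-related MI (type 4a, universal definition), worsening renal function or haemodialysis during the index hospitalisation". I read the index-hospitalisation window as covering the whole list, as the safety hypothesis does.
- **Abstract:** "The primary safety outcome is the composite of bleeding, stroke, procedure-related myocardial infarction and worsening renal function". There is no death component here either, so the omission is not a slip in one place.
- **Efficacy composite:** "Defined as all-cause mortality, rehospitalisation for refractory ischaemia/angina, MI or hospitalisation for HF", followed until the last randomised patient has completed 18 months.
- **Definitions of adverse events:** death is classified by cause, including "death due to stroke, death due to extra-axial haemorrhage, death due to cardiovascular operation". No category is linked to the safety composite. Major bleeding is tied to the BARC criteria with no range of types.
- **Safety hypothesis** (in Advances in interventional management): "a routine non-invasive approach in patients with NSTE-ACS with prior CABG is associated with a lower rate of adverse events related to safety". This claim is limited to the index admission. The second primary aim (Methods and analysis/design) likewise asks whether the non-invasive strategy is safer because it has fewer major complications.
- **Analysis** (Shorter term safety outcomes): numbers and percentages of patients with events, Fisher's exact tests and exact logistic regression.

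**The concern.** The safety composite is meant to show which strategy does more harm in hospital. As defined, a survivor with a type 2 bleed is an event, while a patient who dies in the same admission without a listed component is a non-event. The most serious in-hospital outcome then lowers the apparent event rate of the arm in which it occurs.

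Early death also removes the chance of a later component, and the stated analysis of simple proportions has nothing to deal with that. If such deaths fell mainly in one arm, the composite would flatter that arm on the trial's own safety question. The pilot is described as a rehearsal for the main trial, so the definition may well be carried forward.

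**Working it through.** The plan has no figure to reproduce: no safety event rate is stated, and the article says that no sample size calculation was made. The check is of the definition, followed by simple arithmetic on its possible effect.

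**1. Which in-hospital deaths score as safety events?**

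| Patient who dies in the index admission | Safety event as worded? |
|---|---|
| With a BARC type 2–4 bleed | Yes, through bleeding |
| With a stroke meeting the definition (which includes subdural haemorrhage) | Yes, through stroke |
| With a type 4a MI | Yes |
| With haemodialysis or an eGFR fall of at least 25% | Yes |
| With a fatal bleed graded outside types 2–4 | No, unless another component is met |
| With none of the above, for example a death at the procedure | No |

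**2. Does early death block other components?** Yes, for at least two. Outside subdural haemorrhage, the stroke definition requires signs or symptoms for more than 24 hours, so a stroke fatal sooner does not meet it as worded. Worsening renal function short of haemodialysis needs a later eGFR value.

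**3. Effect of one uncounted death.** Table 2 gives 31 invasive and 29 conservative patients.

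- Invasive arm: 1/31 = 3.2 percentage points.
- Conservative arm: 1/29 = 3.4 percentage points.
- One such death in each arm: 3.4 − 3.2 = about 0.2 points net, so the contrast hardly moves. Distortion needs an imbalance between arms.

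**4. Illustration with assumed counts (not from the documents).** Start from 4/31 against 2/29 events and add deaths not now counted, all in the invasive arm. Two-sided Fisher's exact test:

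| Deaths added | Invasive | Conservative | p |
|---|---|---|---|
| 0 | 4/31 = 12.9% | 2/29 = 6.9% | 0.67 |
| 1 | 5/31 = 16.1% | 6.9% | 0.43 |
| 2 | 6/31 = 19.4% | 6.9% | 0.26 |
| 3 | 7/31 = 22.6% | 6.9% | 0.15 |

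**5. Chance that the gap is met at all.** Let p be the risk of an in-hospital death with no other component. The chance of at least one is 1 − (1 − p)^n. The range for p is an assumption.

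| p | n = 31 | n = 60 |
|---|---|---|
| 1% | 27% | 45% |
| 2% | 46% | 70% |
| 5% | 80% | 95% |

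**The case against.** The best defence is that the split is deliberate. Mortality sits in efficacy, in-hospital complications sit in safety, and both are co-primary. Every death is therefore a co-primary event. Deaths and their causes are also a pilot objective with blinded adjudication, all serious adverse events are summarised, and reporting the components of both composites is already the first secondary aim. The trial is a 60-patient pilot, not powered for clinical outcomes.

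Much of this stands: deaths are not hidden, and keeping them out of safety is a choice that nothing in the article contradicts. But the efficacy composite pools in-hospital deaths with later deaths, MI and rehospitalisations over at least 18 months, and it serves a hypothesis in the opposite direction. Summaries by organ class are not a comparison of in-hospital harm. The article gives no reason for leaving death out of safety.

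Three stronger readings are tempting and are not supported:

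- **That any fatal bleed or procedural death scores as no event.** Many would score through another component, as the first table shows.
- **That stopping at type 4 certainly excludes fatal bleeding.** The article does not reproduce the BARC scale, and the adjudication charter is not shown. The category "death due to extra-axial haemorrhage, death due to cardiovascular operation" does not settle it either: its haemorrhage term is a narrow one, and subdural haemorrhage is also placed under stroke. What can be said is that the article does not state whether fatal bleeding counts.
- **That the safety count is wrong by some large fraction.** Assuming 2–5% mortality (60 × 0.02 = 1.2 to 60 × 0.05 = 3 deaths) and 10–15% composite events (6 to 9) gives roughly 1/9 = 11% to 3/6 = 50%. All these rates are assumed, and the sum takes every death to have no other component.

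**Conclusion.** The point holds in a limited form. The co-primary safety composite omits death and restricts bleeding to BARC types 2–4. An index-admission death without another listed component is therefore not a safety event, and this works against the in-hospital safety hypothesis and the second primary aim. Counting death under efficacy does not repair that contrast.

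The size is unknown from the documents. Each such death in the invasive arm is worth about 3.2 percentage points on the Table 2 allocation. Bias in the comparison arises only if these deaths are unevenly distributed, and the documents do not show that they are or in which direction. The Fisher p values and the probabilities above rest on assumed counts and risks. In an unpowered pilot this is a matter for a modest, inexpensive correction, not a flaw that invalidates the design.

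**What to change.** - Define the analysed safety outcome as any listed component or all-cause death during the index hospitalisation.
- State that a fatal bleed counts as a bleeding event whatever its BARC type, and align the bleeding entry under Definitions of adverse events with the composite.
- Keep the composite as now defined as a sensitivity analysis, and show in-hospital deaths by arm in the component table already planned.
- Table 2 already shows allocated numbers, so date the change and make it before outcomes by arm are examined.

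The cost is outcome wording and one extra analysis, because deaths and causes are already collected and adjudicated. The downside is that an in-hospital death appears in both co-primary composites, so the two are no longer separate counts; say so where the results are reported. If the sponsor prefers to keep death out of safety, the minimum is to give the reason and report the safety outcome with and without in-hospital death.

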### Definitions of adverse events

*Death*: All-cause, sudden cardiac death, death due to MI, death due to HF, death due to stroke, death due to extra-axial haemorrhage, death due to cardiovascular operation, death due to other cardiovascular cause (eg, infective endocarditis), presumed cardiovascular death (undetermined cause of death), non-cardiovascular death.^37^
^38^

*Procedure-related MI:* According to the universal definition of MI. A postprocedure ECG will enable diagnosis of Q versus non-Q MI.

*Stroke* is defined as the presence of a new focal neurological deficit thought to be vascular in origin, with signs or symptoms lasting more than 24 h; subdural haemorrhage.

*Major bleeding* is defined according to the BARC criteria.^36^

*Worsening renal function* is defined as deterioration in estimated glomerular filtration rate ≥25% of baseline during the index admission.

*Follow-up and timing of outcome evaluations*: Follow-up (via telephone contact, clinic visits, letter) with completion of quality of life assessments (EQ-5D) will be maintained at six monthly intervals until a minimum of 18 months follow-up has been reached for the final recruited patient. Data will be held for up to 20 years to enable long-term follow-up analyses.

Following randomisation, clinical assessments will involve gathering information from the standard-of-care clinical reviews (end of hospitalisation, 30–42 days and 1 year) and also from clinical contacts recorded in the patients’ medical records. In West of Scotland hospitals, a single system of electronic patient records is used for all hospital attendances and correspondence with primary care.

*Cross-over*: A cross-over between groups is defined as a change of treatment strategy from invasive to non-invasive management, or vice versa. In addition, we predefined cross-over as occurring within 30 days after randomisation.

### Secondary outcomes

Quality of life (EQ-5D assessed at baseline and six monthly intervals for a minimum of 18 months);CCS angina class;Hospitalisation for refractory ischaemia and/or angina: refractory ischaemia/refractory angina, defined as recurrent ischaemic symptoms lasting more than 5 min, while on OMT (at least two antianginal treatments) with documented characteristic ECG changes indicative of ischaemia and requiring an additional intervention. An additional intervention is defined as reperfusion therapy for MI, cardiac catheterisation and insertion of intra-aortic balloon pump or revascularisation procedure (PCI or CABG surgery) within 48 h of the onset of this episode. This definition is in line with the Timing of Intervention in Acute Coronary Syndromes (TIMACS) trial;^37^Repeat invasive management during follow-up;Freedom from coronary and/or bypass graft intervention;Health economics: secondary care costs and procedure-related costs (diagnostic tests, PCI, CABG), hospital bed days including intensive care, high dependency unit, general medical.

### Health economics

Estimate the cost-effectiveness of routine invasive approach versus conservative management for patients with NSTE-ACS with prior CABG;Identify where additional information in a future trial will have the most value in increasing confidence in net monetary benefit to the NHS.Secondary care and procedure-related costs (diagnostic tests, PCI, CABG), hospital bed days (including intensive care, high dependency unit, general medical) will be recorded prospectively for index and subsequent hospitalisations. This information will be used to provide preliminary information on health economics.

Early estimates of cost-effectiveness may exhibit a large degree of decision uncertainty. Designing a definitive trial to assess the relative clinical and economic outcomes is challenging given the paucity of evidence. Important considerations to consider are: whether it is needed, sample size, length of follow-up and relevant economic outcomes. Preliminary economic modelling and value of information methods can help identify where additional information in a future trial will have the most value.^32–34^ The following section describes the methods to be used in the economic evaluation. The proposed plan follows guidance published by the National Institute for Health and Care Excellence (NICE).^39^

The economic evaluation will be a cost-utility analysis will full incremental analysis.

### Perspective, time horizon, discount rate

The analysis will be conducted from the perspective of the NHS and Personal Social Services (PSS). Differences in major adverse cardiac events may result in lifetime differences in cost and health effects. Thus, the analysis will use a lifetime time horizon. A 3.5% discount rate will be used for both health and cost effects.

Value of information methods used to identify which outcomes affect the probability of cost-effectiveness and likelihood of NHS adoption under commonly used decision thresholds (£20 000–£30 000/QALY).^32–35^ Value of information analyses will also be used to estimate the optimal sample size of a future definitive trial.

*Statistics*: The Robertson Centre for Biostatistics will act as an independent coordinating centre for data management and conduct statistical analyses. The Centre is registered with a Clinical Trials Unit (National Institute for Health Research (NIHR) Registration number: 16). Summary statistics will be performed with data from the pilot study and registry. The proportions of patients with adverse events will be assessed with a χ^2^ test. Summary analyses will be performed on the screening log data.

### Statistical analysis plan

#### Baseline data

Baseline characteristics of the randomised participants (split by randomised group) and for the registry participants will be summarised using mean (SD for continuous measurement), or median (lower quartile, upper quartile for skewed data) and count per cent for categorical variables. Baseline characteristics for randomised participants and registry participants will be compared using t tests, Mann-Whitney tests and χ^2^ tests (or Fisher’s exact tests) as appropriate.

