**Figure 1 OPENHRT2015000371F1:**
[figure not shown]
Flow diagram of Coronary Artery Bypass Graft-Acute Coronary Syndrome (CABG-ACS) trial. Patients who provide consent will enter either the (1) randomised trial or (2) registry (ie, based on the presence of exclusion criteria, or physician or patient preference). Patients who do not provide consent and/or are ineligible will enter the (3) screen failure group. A change in the treatment strategy (eg, from non-invasive to invasive management, or vice versa) within the first 30 days from randomisation is a cross-over.

*Primary aims*: (1) Compared with routine non-invasive management, to assess if a routine invasive strategy is more effective in symptomatic patients with prior CABG compared with OMT; (2) compared with routine invasive management, to assess if a routine non-invasive strategy is associated with fewer major complications and hence is safer; (3) to prospectively quantify resource utilisation in the NHS with each treatment strategy, derive the difference in the quality-adjusted life years (QALYs) and hence provide preliminary health economic information.

*Secondary aims*: To evaluate: (1) the components of the primary composite outcomes for efficacy and safety; (2) quality of life (EuroQol 5 Dimensions (EQ-5D) at baseline and six monthly intervals for a minimum of 18 months); (3) Canadian Cardiovascular Society (CCS) angina class at baseline and six monthly intervals for a minimum of 18 months; (4) repeat invasive management during follow-up; (5) freedom from coronary and/or bypass graft intervention; (6) secondary care costs; (7) the nature and extent of multimorbidity during the index hospitalisation; (8) the nature and extent of native coronary artery and graft disease, including culprit lesion characteristics; (9) a registry of the patients who were not randomised, including the reasons for not being randomised (physician-directed, patient-directed or both) and their clinical characteristics at enrolment and subsequent outcomes during follow-up.

Accordingly, all invasive coronary interventional procedures will be reported:
Elective;Non-elective unplanned (as adjudicated by the CEC).

*Health economics*: Quality of life, direct healthcare costs, adverse events and their economic consequences over a patient's lifetime are key considerations to inform whether or not a routine conservative approach would be acceptable in patients with NSTE-ACS with prior CABG.^12^

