*Registry*: Information will be prospectively recorded in a registry for patients with an acute NSTE-ACS and prior CABG who are not randomised. The reasons for non-participation in the randomised trial will be prospectively recorded. The reasons may be the presence of exclusion criteria, unsuitability for either invasive or non-invasive management, physician preference, patient preference, or a combination of these factors. The registry information will provide insights to reflect an ‘all-comers’ real-world population. The registry will also inform on the feasibility of a future substantive randomised trial. The baseline information and the follow-up assessments are intended to be collected in the same way for the registry and randomised trial participants. Information (clinical characteristics, invasive and non-invasive tests, health outcomes and quality of life during follow-up) in the registry patients will be obtained in the same way as the trial patients, that is, with case note review, telephone contact or a hospital visit and during the longer term by electronic record linkage.

*Screen failure*: For screened patients who are (1) eligible but do not consent to participate in the randomised trial or registry, or (2) ineligible, then the reason(s) for not participating will be documented. No further clinical information will be recorded.

*Sample size calculation*: The sample size in the CABG-ACS pilot trial is n=60 patients. We chose this number in order to gain reasonably representative information on the characteristics of patients with NSTE-ACS with prior CABG in contemporary practice to be enrolled in different secondary care settings in order to be representative of the diversity in UK hospitals. We included four hospitals differing in geographic location, availability of catheter laboratory facilities onsite (or not), and hospital type (academic vs regional).

The sample size was selected to enable the feasibility of randomisation, and the reasons for not being randomised were to be prospectively assessed on multiple occasions. As this pilot was an exploratory, proof-of-concept trial, a sample size calculation was not performed. The trial was designed but not powered to assess for between-group differences in the rates of the primary outcome.

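### The planned randomised-versus-registry test mixes eligibility exclusions with preference among eligible patients, so it cannot alone show whether randomised patients resemble those a similar future trial would recruit

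*Protocol article*

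**What the plan says.** The Baseline data section of the Statistical analysis plan summarises the randomised patients by arm and the registry as one column, then fixes a test between the two populations: "Baseline characteristics for randomised participants and registry participants will be compared using t tests, Mann-Whitney tests", with chi-square or Fisher's exact tests for categorical traits. It names no subdivision of the registry.

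Three places describe who is in the registry:
- Abstract, Methods and analysis: "Patients not randomised due to lack of eligibility criteria and/or patient or physician preference and who give consent will be included in a registry".
- Figure 1 caption: entry to the registry is "based on the presence of exclusion criteria, or physician or patient preference".
- Registry paragraph: "The reasons may be the presence of exclusion criteria, unsuitability for either invasive or non-invasive management, physician preference, patient preference", or a combination. It also says these reasons are recorded prospectively.

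The same article routes ineligible patients elsewhere as well. The Figure 1 caption adds: "Patients who do not provide consent and/or are ineligible will enter the (3) screen failure group". The Screen failure paragraph also lists ineligible patients and says of that group: "No further clinical information will be recorded".

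The Registry paragraph gives two purposes: a picture of the all-comers population, and "The registry will also inform on the feasibility of a future substantive randomised trial". The Sample size calculation paragraph adds that the 60 patients are meant to "gain reasonably representative information on the characteristics of patients with NSTE-ACS with prior CABG in contemporary practice".

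**The concern.** The registry, as described, can contain two different kinds of patient. Some did not meet Box 1, for example because of refractory ischaemia, cardiogenic shock or unsuitability for invasive management, and could not have entered this trial or a successor with similar criteria. Others met Box 1 and were not randomised because they or their physician preferred a strategy. Only the second kind shows selection among recruitable patients.

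A single test of randomised against registry patients cannot tell the two sources apart, and it can mislead in three ways:
- It can reject only because ineligible patients differ, so the randomised group looks unrepresentative of a pool from which it was fairly drawn.
- Ineligible patients can dilute a real difference among eligible patients.
- Opposite differences in the two parts can cancel.

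The article disclaims power for clinical outcomes, so feasibility and representativeness are among the pilot's main products. This is the only test it names between the characteristics of randomised and non-randomised patients.

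**Working it through.** **No plan figure to reproduce.** The 60 randomised patients were chosen without a sample size calculation, and the article gives no registry size, ineligible share or expected baseline differences. What follows is an illustration.

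**Inputs**
- Randomised patients, n₁ = 60: from the article.
- Registry size, n₂ = 120, with 60 and 200 as a range: assumed.
- Share of the registry not meeting Box 1, f = 25%, 50% or 75%: assumed.
- Shift of ineligible patients from randomised patients, d, and of eligible non-randomised patients, e, in SD units: assumed.
- Two-sided 5% level, SD 1 in both groups: assumed. The small extra variance of a mixture is ignored.

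**Formulas**
- Pooled shift: Δ = f·d + (1 − f)·e.
- Standard error: SE = √(1/n₁ + 1/n₂).
- Rejection probability: Φ(|Δ|/SE − 1.96) + Φ(−|Δ|/SE − 1.96).

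**Worked case: no selection among eligible patients (e = 0), d = 0.5, f = 50%, n₂ = 120**
- Δ = 0.5 × 0.5 + 0.5 × 0 = 0.25.
- SE = √(1/60 + 1/120) = √0.025 = 0.158.
- Δ/SE = 1.58.
- Rejection = Φ(−0.38) + Φ(−3.54) ≈ 0.353, about 35%.
- Eligible-only test: Δ = 0, so rejection is 5% whatever f is.

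**Other cases, registry of 120**

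| Case | Test | f = 25% | f = 50% | f = 75% |
|---|---|---|---|---|
| Only ineligible differ: d = 0.5, e = 0 | Pooled | 12% | 35% | 66% |
| | Eligible only | 5% | 5% | 5% |
| Only ineligible differ: d = 0.8, e = 0 | Pooled | 24% | 72% | 97% |
| | Eligible only | 5% | 5% | 5% |
| Only eligible differ: d = 0, e = 0.5 | Pooled | 66% | 35% | 12% |
| | Eligible only | 85% | 78% | 61% |

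The eligible-only row of the last case compares 60 randomised patients with 90, 60 or 30 registry patients. At 60 against 60, SE = √(2/60) = 0.183, 0.5/0.183 = 2.74, and Φ(0.78) ≈ 0.78.

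**Cancellation.** With d = 0.5, e = −0.5 and f = 50%, Δ = 0. The pooled test rejects 5% of the time although the eligible patients truly differ. The eligible-only test has 78% power.

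**Registry size.** For d = 0.5, e = 0 and f = 50%, pooled rejection is 28% with 60 in the registry and 40% with 200. If f = 0 it is 5% at any size: the problem disappears if the registry holds no ineligible patients.

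**The case against.** The strongest reply is that the pooled comparison is what the registry was set up for. The Registry paragraph puts the all-comers picture first, and the sample size rationale also refers to patients in contemporary practice and not only to those meeting Box 1. Against that purpose a comparison with the whole registry is sensible. This stands, and it is why the pooled summary should be kept.

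A reader might infer something stronger: that the p value reflects Box 1 exclusions instead of selection, and that its null hypothesis is false by design. The article does not support this.
- The ineligible share is not given. If it is small, the p value mainly reflects preference.
- The Consent paragraph requires written consent from registry patients, so those barred for inability to consent cannot be in it.
- The Figure 1 caption and the Screen failure paragraph also send ineligible patients out of the registry. Secondary aim 9 describes the reasons for non-randomisation only as physician-directed, patient-directed or both.
- A built-in difference is certain only for traits that define exclusion, not for every baseline variable.

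It can also be said that a breakdown by reason may be in a full analysis plan that is not shown, that the pilot objectives already include reporting the reasons, and that no decision rule depends on this test. All three are fair and limit the weight of the point. They do not remove it: the article itself names the comparison and the tests, and the one it names does not isolate the group most relevant to a future trial's recruitment.

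**Conclusion.** The point holds in a limited form. The planned test mixes eligibility exclusions with selection among recruitable patients. It serves the all-comers purpose, but cannot by itself show whether randomised patients resemble the eligible patients whom a similar future trial would recruit.

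The size is unknown because the ineligible share is unknown. In the illustrations with a 0.5 SD shift in ineligible patients only and 120 in the registry, the pooled test rejects 12% to 66% of the time as the ineligible share goes from 25% to 75%. Everything except the 60 randomised patients is assumed.

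The conflict over where ineligible patients go adds to the uncertainty. One could read the screen failure wording as meaning ineligible for the registry too, or ineligible and without consent, but the text does not say so. Until it does, the composition of the registry, and so the meaning of its p value, is not fixed.

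The consequence is confined to the feasibility and representativeness output. The randomised comparison is not touched. This is an inexpensive improvement, not a serious defect.

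**What to change.** In the Baseline data section:
1. Keep the pooled registry summary, labelled as the all-comers description.
2. Add a comparison of randomised patients with registry patients who met Box 1 but were not randomised because of patient or physician preference. Report differences with 95% CIs (standardised for continuous traits, risk differences for binary ones), so that a non-significant result is not read as similarity.
3. Show registry patients who had an exclusion criterion, or were otherwise ineligible, in a separate descriptive column. State in advance how patients with both an exclusion criterion and a preference are classed. Counting them as ineligible keeps the group in step 2 clean.

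Separately, reconcile the Abstract, the Figure 1 caption and the Registry and Screen failure paragraphs on whether ineligible patients enter the registry or the screen failure group.

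**Cost.** A few sentences and one or two table columns, with no new data, because the reason for non-randomisation is already to be recorded. The price is a smaller comparison group and wider intervals. With 120 in the registry, the 95% CI half-width for a standardised difference is 1.96 × √(1/60 + 1/120) = 0.31 SD for the pooled group. If half are eligible it is 1.96 × √(1/60 + 1/60) = 0.36 SD, and if a quarter are, 1.96 × √(1/60 + 1/30) = 0.44 SD.
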